**Amendment 21 May 2015**

The following amendment is proposed

1. Health Survey for England estimates that currently 1.4 million residents in England are morbidly obese (BMI > 40kg/m2 ). For all outcomes where surgery appeared to have an effect, we will estimate the absolute number of outcomes that surgery could potentially prevent, by applying the relative risks obtained in our analysis to the rate of events detected in the non-surgery group, and scaling to 1.4 million people.
2. In order to maximise the study population size, we will no longer use MINAP and HES to ascertain MIs and will instead use first recorded MI in the CPRD GOLD record.

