**Specific Aims**

Rates of the following outcomes will be compared between groups: Mortality, post-operative complications, type 2 diabetes, cardiovascular disease, fractures, cancer, fatty liver, acute liver injury and obstructive sleep apnoea. Changes over time will be compared against baseline and between groups for the following outcomes: weight, body mass index (BMI), lipid profile.

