**Sample Size/Power Calculation**

Counts received from the GPRD show:

- ~2,000 registered patients have had bariatric surgery, with a mean follow up of 2.4 years
- ~80,000 patients have received a prescription for orlistat
- >1.4 million patients have a BMI >=30

QRESEARCH contains data on a similar number of patients to GPRD and we therefore anticipate the number of eligible patients for this study would be roughly double the numbers shown above.

Assuming we match 5 untreated patients to each patient with an obesity intervention, we would have 80% power to detect a reduction in mortality over 4 years amongst those undergoing surgery from 5% to 3.9% (over the whole 4 year period).

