For exposure to orlistat, follow up time will be censored 3 months after the date when prescribing information indicates treatment was stopped. This period allows for a degree of medication stockpiling and a treatment washout period. Similarly, follow up time for controls matched to orlistat recipients will be censored at the same date ensuring similar follow up in comparison groups.

Sensitivity analyses will stratify orlistat exposure on dose and duration using recorded prescribing information to estimate daily dose and duration of treatment.

Where possible, we will calculate number needed to treat (NNT) or number needed to harm (NNH) for clinical outcomes where a treatment effect is seen.

Linear regression will be used to compare changes in weight and BMI between surgical or pharmacological interventions and no intervention, adjusting for the propensity score. Changes will be calculated annually.

Similarly, a paired t-test will be used within each treatment group to determine changes in weight and BMI from baseline (pre-intervention). Changes will be calculated annually.

Absolute rates will also be determined for post-operative complications (post-operative haemorrhage, post-operative infection, ITU admission, re-admission to hospital and re-operation). Cox regression will be used to compare the hazard for each event between different types of bariatric surgery.

Initially the analysis will be done separately for QRESEARCH and GPRD data. It is anticipated the results will be very similar since the two datasets represent different samples of the same underlying population. Assuming the results are similar, data will be pooled, and a single analysis will be done, which will increase precision.

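### The 1.4 million extrapolation and the NNT/NNH depend on an undefined, result-based trigger; displayed effects can be exaggerated, and null or harmful outcomes drop out of the national figure

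*Protocol*

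**What the plan says.** Three parts of the protocol bear on this.

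- **Amendment 21 May 2015, item 1.** The extrapolation is conditional: "For all outcomes where surgery appeared to have an effect, we will estimate the absolute number of outcomes that surgery could potentially prevent". The method is to proceed "by applying the relative risks obtained in our analysis to the rate of events detected in the non-surgery group, and scaling to 1.4 million people". No p-value, confidence-interval rule or effect size defines the condition, and the item speaks only of prevention.
- **Statistical Analysis and Covariates, cohort analysis.** Subject to feasibility, the plan is that "we will calculate number needed to treat (NNT) or number needed to harm (NNH) for clinical outcomes where a treatment effect is seen". This covers benefit and harm, but the condition is again undefined.
- **Specific Aims.** The comparisons themselves carry no such condition: "Rates of the following outcomes will be compared between groups: Mortality, post-operative complications, type 2 diabetes, cardiovascular disease, fractures, cancer, fatty liver, acute liver injury". Sleep apnoea is on that list too.

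So every listed outcome is to be compared, but only those that pass an unstated test are turned into absolute numbers.

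**The concern.** If an estimate is shown only because it looked large enough, its average over repeated studies lies further from the null than the true effect. The weaker the power, the larger the gap. Here many outcomes and sub-outcomes are compared, no multiplicity control is stated, and whoever reads the results decides what qualifies.

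The national figure has a second problem. It is defined only as events that surgery could prevent. If surgery raised the rate of a listed event, fractures for instance, the extrapolation would have no line for the events caused. A reader adding up the lines would see benefits without offsetting harms and without the outcomes where nothing was found.

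At stake is a set of absolute numbers scaled to 1.4 million people. The relative comparisons are not affected.

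**Working it through.** **The plan's own figures.** The protocol gives no number for prevented events, NNT or NNH, so there is none to reproduce. Its only surgery calculation is a power statement: 80% for four-year mortality of 5% against 3.9%. With 5:1 matching and two-sided 0.05 (assumed, since alpha is not stated), a pooled two-proportion calculation gives 86.2% at 4,000 surgery patients and 74.5% at 3,000; exactly 80% needs 3,408. That mismatch is a separate matter. The statement serves here only for the effect it implies: HR = ln(0.961)/ln(0.95) = 0.776.

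**Inputs**
- Surgery patients: 3,000 (the amendment restricting the study to CPRD says more than 3,000).
- Comparators: 15,000, from "Assuming we match 5 untreated patients to each patient with an obesity intervention".
- Mean follow-up: 2.4 years, from "2,000 registered patients have had bariatric surgery, with a mean follow up of 2.4 years".
- Comparator mortality: 5% over 4 years (Sample Size/Power Calculation).
- Assumed: constant hazard, full matching, normal log HR, and a trigger of two-sided p<0.05 in the direction of benefit.

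**Formulas**
- Comparator rate r = -ln(0.95)/4 = 0.01282 per year.
- Deaths: d1 = 3,000 × 2.4 × r × HR; d0 = 15,000 × 2.4 × r = 462.
- s = SE(log HR) = √(1/d1 + 1/d0).
- With θ = ln HR and cut-off c = -1.96s, mean displayed HR = exp(θ + s²/2) × Φ((c-θ-s²)/s) / Φ((c-θ)/s).
- Prevented per year = 1,400,000 × r × (1-HR) = 17,953 × (1-HR).

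**Worked case, true HR 0.90.** d1 = 83, s = 0.119, c = -0.234. Probability of display = Φ(-1.076) = 0.141. Mean displayed HR = 0.9064 × 0.116/0.141 = 0.746. Displayed: 17,953 × 0.254 = about 4,560 deaths a year. True: 17,953 × 0.10 = 1,795. Ratio 2.5.

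| True HR | P(displayed) | Mean displayed HR | Displayed per year | True per year | Ratio |
|---|---|---|---|---|---|
| 1.00 | 0.025 | 0.767 | 4,190 | 0 | – |
| 0.90 | 0.141 | 0.746 | 4,560 | 1,795 | 2.5 |
| 0.78 | 0.50 | 0.707 | 5,260 | 3,950 | 1.3 |
| 0.50 | 0.994 | 0.504 | 8,900 | 8,980 | 0.99 |

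**Sensitivity to size and follow-up at the protocol's own effect (HR 0.776).** The ratio is 1.07 with 4,000 surgery patients and 4 years, 1.14 with 3,000 and 4 years, 1.31 with 3,000 and 2.4 years, and 1.50 with 2,000 and 2.4 years.

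**Sensitivity to the trigger.** Suppose an apparent effect means only an estimated HR below 1. A true HR of 0.90 then gives about 2,360 a year against 1,795 (1.3 times), and a true null, displayed half the time, gives about 1,520 against 0. The bias therefore does not need a significance rule.

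**What an interval would show.** At an estimated HR of 0.78, s = 0.127 and the 95% limits are 0.61 to 1.00. Before allowing for uncertainty in the comparator rate, the number prevented runs from about 0 to 7,030 a year around the central 3,950.

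**The case against.** A reader might infer that the figures are selected on statistical significance and must overstate benefit. The text does not support that. No threshold is stated, and the size of the bias cannot be derived from the protocol alone. It is close to nil for strong effects, and the largest ratios belong to cases that would seldom be displayed (14% and 2.5% of the time). For NNH, selection would exaggerate harm, not benefit. Nor does the protocol rank the extrapolation above the hazard ratios, so calling it the headline result would go too far.

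Null and harmful results also stay in the plan. All outcomes are compared without a filter, NNH is provided for, and absolute rates of post-operative complications are unconditional. Silence on intervals does not exclude them, and such detail is commonly left to a statistical analysis plan.

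The illustration has limits too. It joins a follow-up figure from the earlier count to the later patient count. It uses a 5% mortality set when comparators needed only BMI above 30, whereas the first amendment now draws matches for surgery from BMI of 40 or more. It covers mortality alone.

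Finally, reporting every outcome does not shrink any single estimate: an observed HR of 0.746 still converts to about 4,560.

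Most of this stands, and it limits the claim. It does not remove the defect: the protocol itself writes a result-dependent rule, which is more than missing detail. Unfiltered relative comparisons do not repair an absolute summary built from a filtered set. A full list removes selection from that set, and intervals show how uncertain each line is.

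**Conclusion.** The concern holds in a limited form. The trigger for the national extrapolation and for NNT/NNH is undefined and depends on the results. The extrapolation, as worded, also has no place for null or harmful outcomes. Displayed absolute effects can therefore be exaggerated when power is modest.

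For mortality, under the assumed p<0.05 filter with 3,000 surgery patients and 2.4 years, the exaggeration is about 1.3 times at a true HR of 0.78, 2.5 times at 0.90 and negligible at 0.5. These figures rest on the assumptions listed above; other outcomes were not modelled. The relative estimates are untouched. The rule should nonetheless be changed, because figures scaled to 1.4 million people should not hang on an unspecified choice made after the results are known.

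**What to change.** **Amendment 21 May 2015, item 1.** Replace the condition with a list fixed in advance of incident adverse events compared between surgery and no treatment: for example death, first diabetes diagnosis, MI, stroke, angina, hypertension, fractures, cancer, fatty liver, acute liver injury and sleep apnoea. Scale each to the part of the 1.4 million at risk of it. Report the number prevented or caused for every one, whatever the result, with 95% limits carried through from both the relative risk and the comparator rate (delta method or bootstrap).

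Omit or report separately diabetes resolution, improvement of hypertension and progression of diabetes treatment. These need their own denominators and cannot be scaled to all 1.4 million, so a list of every outcome would be wrong.

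**Statistical Analysis and Covariates.** Report absolute risk differences with 95% confidence intervals for the same listed outcomes, and give NNT/NNH as a supplement. The risk difference should lead because an NNT interval splits into two disjoint parts when the effect interval includes the null.

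**Cost.** No new data are needed, only a few more table rows and an interval calculation. Some intervals will be wide or include no benefit.

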**Study Design and Study Population**

A combination of two UK databases offers an excellent opportunity to study the clinical effects of interventions for obesity; the UK General Practice Research Database (GPRD) and QRESEARCH. In combination the GPRD and QRESEARCH contain information from >1100 UK general practices, and have current and historical data for >20 million patients. Continuous patient records include details of all consultations, diagnoses, prescribed medicines and basic demographic data. Patients are representative of the England & Wales population in terms of age, sex and geographical distribution [refs]. Data quality is subject to rigorous checks and audits and >500 peer reviewed studies have been published using GPRD or QRESEARCH data including studies investigating unintended effects of medication (GPRD, 2010; QRESEARCH, 2010). GPRD and QRESEARCH draw information from mutually exclusive practices and are therefore fully complementary.

*3.1 Study Design - Patient population, exposures of interest, inclusion/exclusion criteria*

The cohorts will comprise obese patients registered in the GPRD and QRESEARCH:

- Eligible patients will be those aged 18+ years with at least 12 months research standard registration time in the GPRD or QRESEARCH AND with one of the following exposures recorded by the study start:
  - A record of bariatric surgery with at least 12 months prior registration to ensure incident status (specific type of bariatric surgery used will be determined using data recorded in patient records); OR
  - A first prescription for orlistat with at least 12 months prior registration to ensure incident usage; OR:
  - A record of BMI>30 with neither bariatric surgery nor a prescription for orlistat – these patients will act as the **comparison group**
- The date of surgery or first orlistat prescription will be termed the index date. Each patient with surgery or orlistat will be matched with up to 5 obese patients without a record of these treatments, on age (within 5 years), sex and practice with at least 12 months research standard registration prior to the relevant index date.
- Patients will be followed until the earliest of; an outcome of interest, death, transfer out of the practice or last data collection date.

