**Statistical Analysis and Covariates**

*Baseline Comparisons*

We will use baseline data to compare the background characteristics of patients receiving surgical and pharmacological interventions for obesity with those receiving no intervention. This will give a broad picture of how these interventions are being targeted in the UK as a whole. Odds ratios and 95% confidence intervals will allow us to determine statistically and clinically relevant differences, using patients with no intervention as the baseline group. As a subgroup analysis, differences in the targeting of specific forms of bariatric surgery will also be determined. **Covariates** to be assessed will include age, sex, weight, BMI, smoking status, alcohol consumption and a range of co-morbidities such as coronary heart disease, hypertension and diabetes.

*Cohort analysis*

We will compare outcomes between patients receiving surgical and pharmacological interventions for obesity with those receiving no intervention. It is anticipated that these three groups of patients will differ in fundamental ways related to health outcomes that could represent important bias and confounding in this study. For this reason we will calculate propensity scores for each patient, capturing their likelihood to receive either surgery or a prescribed anti-obesity therapy. Using the propensity scores we will ensure comparisons are only made between patients with similar background characteristics (Sturmer et al, 2010). Cox proportional hazard regression will be used to conduct time to event analyses for death, diabetes, cardiovascular disease, fractures and liver disease, adjusting for the propensity score. Patients with no intervention will form the baseline group.

In addition, anonymised, linked Hospital Episode Statistic (HES) data are available for patients in the GPRD and will allow us to look in detail at hospital records for patients who undergo bariatric surgery (e.g. type of surgery, any complication that arise).

Patients who receive orlistat and later have surgery will move from one exposure group to the other, according to current treatment. We anticipate that very few patients will receive orlistat following surgery and any patients who appear to do so will be excluded from the analysis.

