**Amendment**

A number of amendments to this protocol are now sought:

1. Due to funding constraints, it will not be possible to access QRESEARCH data and the study will be restricted to CPRD data only. We do not anticipate major changes to the feasibility of the study, as the current number of patients in the CPRD with bariatric surgery is now >3,000.
2. Following initial data processing it became apparent that matches for bariatric surgery patients, drawn from the population of patients with a BMI >30 were very dissimilar from the surgery patients, mainly because the surgery group tended to have a much higher BMI. Since the guidelines for surgery include a requirement of BMI >=40 in most instances, we propose matches to be drawn from a pool of patients with any measure of BMI >=40 during their registration.
3. For the analysis of weight loss, we intend to measure the effects to a maximum of three years post-intervention, largely driven by the amount of follow up available for surgery patients
4. Following statistical advice from [name], it was decided that mixed effects linear regression should be used to assess changes in weight and BMI over time within each group. We anticipate a non-uniform rate of change over follow up and will model this using splines. The Akaike Information Criterion (AIC) will be used to determine optimal spline knot points. From the final model, weight/BMI and 95% confidence intervals for the study population will be estimated. The rate of change in weight or BMI and 95% confidence intervals will be calculated for each spline component.
5. For all other outcomes, orlistat patients will be censored at the end of follow up, analogous to an intention to treat type analysis, so the long term consequences of the decision to start a course of treatment with orlistat can be measured, regardless of subsequent treatment. As a sensitivity analysis, follow up will be censored at the estimated date treatment was stopped, based on prescribing records.
6. Subgroup analyses according to underlying diabetes and cardiovascular disease status will be carried out, in line with NICE recommendations for research on treatments for obesity. Additionally, where numbers permit, analyses of bariatric surgery patients will be stratified by surgery type.
7. As a clarification, patients who have bariatric surgery and later receive orlistat will be excluded from orlistat analyses only.

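### The national count of preventable events scales the crude event rate of comparators matched to surgery patients, with no step to re-weight it to the age and sex of the 1.4 million

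*Protocol*

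**What the plan says.** The Protocol's Amendment 21 May 2015, item 1, cites a survey estimate that "1.4 million residents in England are morbidly obese", meaning a BMI above 40. For every outcome on which surgery appears to act, it will compute a number of preventable events "by applying the relative risks obtained in our analysis to the rate of events detected in the non-surgery group, and scaling to 1.4 million people". No age or sex weighting is mentioned.

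The non-surgery group is built in section 3.1 of Study Design and Study Population: "Each patient with surgery or orlistat will be matched with up to 5 obese patients without a record of these treatments", and the matching is "on age (within 5 years), sex and practice with at least 12 months research standard registration". Item 2 of the earlier Amendment changes the source of the matches for surgery patients: "we propose matches to be drawn from a pool of patients with any measure of BMI >=40 during their registration". It leaves the matching variables as they were.

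Statistical Analysis and Covariates expects that the "three groups of patients will differ in fundamental ways related to health outcomes".

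**The concern.** Matching on age and sex serves the relative risk: it makes the comparators resemble the people who had surgery. For the same reason it makes their absolute event rate specific to that age-sex mix. The 2015 amendment then uses this rate as if it belonged to all morbidly obese residents.

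Death, myocardial infarction, stroke, cancer and fracture all vary with age and sex. If people who have surgery differ in age or sex from the 1.4 million, the count of preventable events is wrong for each such outcome. The problem is separate from who is at risk for a given disease, because it also affects all-cause death, where everyone is at risk. What is at stake is the absolute count, not any hypothesis test or hazard ratio.

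**Working it through.** **The plan's own figure.** The protocol states no number of preventable events, so there is nothing to reproduce. What can be checked is the rule.

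**The rule as written.** With N the target size, r0 the comparator event rate and RR the relative risk:

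prevented = N × r0 × (1 − RR)

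**The rule the target requires.** With w_s the share of the target in age-sex stratum s and r0_s the untreated rate in that stratum, and a common RR as the plan implies:

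prevented = N × Σ(w_s × r0_s) × (1 − RR)

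The two agree only if the comparators' own mix gives the same average rate as the target's mix. Matching ties the comparators' mix to that of surgery patients, approximately, since age may differ by up to 5 years and the number of matches may vary.

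**Proportionality.** The only comparator risk and surgery effect in the protocol are in Sample Size/Power Calculation: mortality falling "from 5% to 3.9% (over the whole 4 year period"). They serve here only as arithmetic.

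- N = 1,400,000; r0 = 0.05; RR = 3.9/5 = 0.78
- As written: 1,400,000 × 0.05 × 0.22 = 15,400 over 4 years
- True average rate 0.75 times the matched rate: 15,400 × 0.75 = 11,550
- True average rate 1.5 times the matched rate: 15,400 × 1.5 = 23,100

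**How a difference in mix acts.** Every stratum value here is an assumption. Take 4-year mortality of 1.5%, 5% and 15% at ages 18–44, 45–64 and 65+, and a surgery-matched mix of 50/47/3%.

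- Matched rate: 0.50 × 1.5 + 0.47 × 5 + 0.03 × 15 = 3.55%
- Count as written: 1,400,000 × 0.0355 × 0.22 = 10,934

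| Assumed target mix (%) | Average rate | Count | Ratio to 10,934 |
|---|---|---|---|
| 50/47/3 | 3.55% | 10,934 | 1.00 |
| 55/43/2 | 3.275% | 10,087 | 0.92 |
| 40/45/15 | 5.10% | 15,708 | 1.44 |
| 35/40/25 | 6.275% | 19,327 | 1.77 |

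The table shows that the error can go either way, and that it vanishes when the mixes agree. It does not estimate the error in this study.

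**The case against.** Several counter-arguments have force.

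- **No distributions are given.** The protocol reports no age or sex distribution for surgery patients, comparators or the 1.4 million. A reader might infer that the national count is shown to be wrong in a known direction, or by a stated factor. For instance, mortality rising 6–10% per year of age with mean ages 3–10 years apart gives exp(0.06 × 3) = 1.20 to exp(0.10 × 10) = 2.72. The protocol does not support that range: the 3-year minimum gap is an assumption that excludes a small error, and with no gap the factor is 1. This objection stands in full.
- **The 15,400 is not a forecast.** The 5% and 3.9% are a power scenario written when the pool was BMI above 30 and a second database was included. The amendment would use observed rates. This also stands.
- **The pool is already restricted on BMI.** The earlier Amendment brings the comparators broadly into line with the target on BMI. True, but it does nothing for age and sex.
- **The detail may sit elsewhere.** The amendment is brief, does not define the non-surgery group, and does not call the rate crude; an analysis plan might add standardisation. But it is more than silent: it names the rate to use and the number to scale it to. The matched group is the only non-surgery group that the protocol describes for the surgery comparison. If another was meant, the text needs correcting anyway.
- **The quantity is secondary and worded as potential.** No objective or test depends on it. That limits the importance, but cautious wording about causation does not change which rate is multiplied.

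**Conclusion.** The point holds as a defect in the stated rule. Followed literally, item 1 gives a count for a population with the surgical age-sex mix and attaches it to all 1.4 million. The count is biased unless that mix gives the same average event rate as the target's. The protocol neither claims nor shows that it does.

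Direction and size cannot be established from the protocol. What can be said is that any relative error in the rate passes in full to the count, for every outcome that is scaled. The conclusion rests on reading the non-surgery group as the matched comparators and their rate as unweighted, which is the natural reading of the text. The relative risks and the between-group comparisons are untouched. The rule should be changed before the count is reported, but the main analysis does not depend on it.

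**What to change.** In the Amendment 21 May 2015, item 1, replace the crude non-surgery rate as follows.

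1. Estimate age- and sex-specific event rates in the existing matched comparators with BMI of at least 40.
2. Standardise these rates directly to the age-sex distribution of morbidly obese residents from the Health Survey for England. If that is not available, use the distribution of the untreated CPRD pool with BMI of at least 40, and state the assumption that this pool represents the target.
3. Scale only to the age-sex strata in which both surgery patients and comparators occur, and reduce the 1.4 million accordingly.

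Using the matched comparators for the rates avoids a further problem. They already have index dates from their matched patients, whereas rates from the whole unmatched pool would need a new rule for the start of follow-up.

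The cost is a sentence or two in the amendment and a short calculation on data already held, plus a source for the target distribution. The estimate becomes slightly more complex, less precise where strata are thin, and possibly smaller.

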**Outcomes**

Outcomes have been chosen as events that are well recorded by GPs as part of routine patient care, regardless of where a diagnosis is made (by the GP or in secondary/tertiary centres). Numerous studies have been published looking at these outcomes using data from the GPRD/QRESEARCH and validity has been shown to be high (GPRD, 2010; QRESEARCH, 2010). The following outcomes will therefore be ascertained for all patients in the cohort:

- Death
- Change in Weight
- Change in BMI
- Diabetes
  - First diagnosis
  - Progression to monotherapy with oral antidiabetic agent
  - Progression to polytherapy with oral antidiabetic agents
  - Progression to insulin therapy
  - Resolution (noted in GP record as patient removal from diabetes QOF register)
- Cardiovascular disease
  - Incident MI
  - Incident stroke
  - Onset of hypertension
  - Onset of angina
  - Improvement of hypertension determined by permanently stopping antihypertensive medication, i.e. at least 6 months without a further prescription
- Osteoporotic Fractures (hip, spine, wrist)
- Acute liver injury as indicated by a diagnostic code or a record of alanine transferase at >3X upper limit of normal in patients without chronic liver disease.
- Fatty liver
- Incident cancer diagnoses
- Obstructive sleep apnoea
- Change in lipid profile

In addition, within the GPRD, Hospital Episode Statistics (HES) data will be available for a large proportion of the cohort. We will therefore be able ascertain post-operative outcomes, including post-operative haemorrhage, post-operative infection, ITU admission, re-admission to hospital and re-operation. Also, within the GPRD, detailed information on acute coronary events will be available via linkages with the Myocardial Ischaemia National Audit Project (MINAP).

The research team has considerable experience in developing algorithms for determining outcomes based on both GPRD and is developing expertise with HES data – algorithms for specific outcomes are available on request.

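### The population-impact rule applies every event rate to all 1.4 million morbidly obese people, although many of the outcomes can occur in only part of them

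*Protocol*

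**What the plan says.** All references are to the Protocol.

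- **Amendment 21 May 2015, item 1** sets the target population: "Health Survey for England estimates that currently 1.4 million residents in England are morbidly obese". It then fixes the scope: "For all outcomes where surgery appeared to have an effect, we will estimate the absolute number of outcomes that surgery could potentially prevent". The method is "applying the relative risks obtained in our analysis to the rate of events detected in the non-surgery group, and scaling to 1.4 million people". It names no at-risk fraction, rate denominator or time horizon.
- **Outcomes** defines the events. Diabetes is listed as "First diagnosis" and then as three steps of drug progression. The blood pressure event is "Onset of hypertension", and angina is worded in the same way. MI, stroke and cancer are incident events. Item 2 of the same 2015 amendment says of MI that the study "will instead use first recorded MI in the CPRD GOLD record".
- **Study Design and Study Population** ends a patient's follow-up at the outcome of interest if nothing else ends it sooner. Treated patients are "matched with up to 5 obese patients without a record of these treatments", on age, sex and practice.
- **Statistical Analysis and Covariates** names Cox regression for the time-to-event outcomes, with the no-intervention group as reference.
- **Amendment, item 2** moves the pool of comparators for surgery to people with a BMI of 40 or more.

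**The concern.** A first diagnosis of diabetes cannot occur in someone who already has diabetes, and progression to insulin cannot occur in someone without it. If a rate is calculated among those who can have the event and is then multiplied by everyone, the product includes people in whom there is nothing to prevent. The rule makes no allowance for this and is the same for every outcome.

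The result is an absolute count for a national population, which readers may take as the scale of benefit from wider use of surgery. The error differs by outcome, so it also distorts the ranking of outcomes: deaths would be counted correctly beside inflated counts for diabetes and hypertension. The hazard ratios themselves are not touched.

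**Working it through.** The Protocol states no prevented-event count, so there is no figure to reproduce.

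**Step 1: who can have each event.** Outcomes lists 16 event-type outcomes, leaving aside changes in weight, BMI and lipids. Two of these (diabetes resolution and hypertension improvement) are benefits rather than events to prevent, which leaves 14.

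- Only without the condition (7): first diabetes diagnosis, incident MI, incident stroke, incident cancer, onset of hypertension, onset of angina, and acute liver injury (restricted to people without chronic liver disease, at least by its laboratory criterion).
- Only with the condition (3): progression of diabetes to monotherapy, to polytherapy and to insulin.
- Everyone (2): death and osteoporotic fracture.
- No explicit restriction (2): fatty liver and sleep apnoea.

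So 7 + 3 = 10 of the 14 are restricted.

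**Step 2: formulas.** Let N = 1.4 million, r the untreated risk or rate among people at risk, RR the relative risk, and p the baseline prevalence of the condition in the 1.4 million.

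- Rule as written, with r per person at risk: N × r × (1 - RR)
- Events possible only without the condition: N × (1 - p) × r × (1 - RR)
- Events possible only with the condition: N × p × r × (1 - RR)

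The ratio of the rule to the correct count is 1/(1 - p) or 1/p. Neither r nor RR enters it.

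**Step 3: numbers.** The documents give no p, so the values are assumed.

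| p | At risk, without condition | Factor 1/(1-p) | At risk, with condition | Factor 1/p |
|---|---|---|---|---|
| 2% | 1.372 million | 1.02 | – | – |
| 10% | 1.26 million | 1.11 | 0.14 million | 10 |
| 20% | 1.12 million | 1.25 | 0.28 million | 5 |
| 30% | 0.98 million | 1.43 | 0.42 million | 3.33 |
| 40% | 0.84 million | 1.67 | 0.56 million | 2.5 |
| 50% | 0.70 million | 2.00 | 0.70 million | 2.0 |

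**Step 4: illustration**, with assumed r = 5% and RR = 0.6. The rule gives 1,400,000 × 0.05 × 0.4 = 28,000 events prevented. For a first-event outcome at p = 20% the correct count is 1,120,000 × 0.05 × 0.4 = 22,400. For an outcome confined to people with the condition, at the same p, it is 280,000 × 0.05 × 0.4 = 5,600.

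**Step 5: an outcome that escapes.** Using the planning risks in Sample Size/Power Calculation (5% falling to 3.9% over 4 years), deaths prevented are 1,400,000 × (0.05 - 0.039) = 15,400. Everyone is at risk of death, so no at-risk correction applies.

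**The case against.** The strongest reply concerns the denominator. The amendment speaks of the rate in the non-surgery group, which can be read as events divided by everyone in that group, prevalent cases included. The rate is then r × (1 - p) and scaling to 1.4 million gives the correct 22,400 in the illustration at p = 20%. This stands as arithmetic, and the text does not exclude it. But it holds only if prevalence in the comparison group equals that in the 1.4 million, which nothing in the Protocol establishes for a group matched to surgery patients. It is also not the natural rate for first events analysed by Cox regression with follow-up ending at the event. On either reading the denominator has to be stated.

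It could also be said that such detail belongs in an analysis plan. Here, however, the Protocol itself sets the rule and the multiplier.

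The 1/p factor for diabetes progression takes people with diabetes at baseline as those at risk. If progression were also counted in people diagnosed during follow-up, the factor would be smaller. If people already on the therapy in question are removed, it would be larger.

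Four stronger readings are tempting but unsupported:

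- **A net upward bias is certain.** The comparison group carries the age and sex mix of surgery patients, and the documents give that mix neither for them nor for the 1.4 million. This second error has no known direction and could offset the first.
- **Diabetes resolution and hypertension improvement are inflated most.** The outcome "Resolution (noted in GP record as patient removal from diabetes QOF register" and its hypertension counterpart are gains. A rule about events prevented does not plainly cover them.
- **Harms are left out.** Statistical Analysis and Covariates plans numbers needed to harm and absolute rates of post-operative complications. They are not netted into this extrapolation, but they are reported.
- **This is the study's main result.** Objectives and Specific Aims concern comparisons between groups. The extrapolation is a later addition in hedged language.

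**Conclusion.** The point holds as a mismatch between the scaling rule and the Protocol's own outcome definitions. With rates per person at risk, which the planned analysis implies but the amendment does not state, prevented events are overstated by 1/(1-p) for first-event outcomes and by 1/p for outcomes confined to people with the condition.

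The arithmetic is exact; the sizes depend on assumed prevalences. The error is material for common conditions such as diabetes or hypertension, and largest for diabetes progression. For conditions with a prevalence of 2% to 10% it is only 1.02 to 1.11 times for first events. Death and fractures are not affected. The finding concerns this one component for the restricted outcomes. It does not establish the net direction of error in the whole estimate, and it leaves the relative comparisons intact.

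**What to change.** Reword item 1 of the 2015 amendment so that, for each outcome:

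1. the untreated rate is calculated among people at risk, and its denominator is stated;
2. that rate is multiplied by the part of the 1.4 million at risk: 1.4 million × (1 - p) for first-event outcomes, 1.4 million × p for diabetes progression (less those already on the therapy concerned), and the full 1.4 million for death and fractures;
3. p comes from baseline records in the BMI >=40 comparison pool, before matching;
4. a time horizon is given, because a rate times a headcount is not a number of events without one.

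Two additions are useful but do not correct a stated error: carry the confidence interval of the hazard ratio through to the count, and standardise the untreated rate to the age and sex mix of the unmatched pool.

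The cost is a short rewording and a small calculation on data the study already uses. Baseline co-morbidity is among the planned covariates, and the Amendment (item 6) already plans subgroups by diabetes and cardiovascular status. No new data collection is needed. The at-risk correction by itself lowers the counts for restricted outcomes; standardisation could move them either way.
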